### Ethical approval and study registration

The Ethics Committee of the Third People's Hospital of Xiaoshan District, Hangzhou, granted ethical approval (Xiaoshan Third Hospital 2022 Research No.: 004) for carrying out this study. Prior to enrollment, each participant will be informed of detailed information about the study, welfare, and possible risks. All participants will be allowed to withdraw from this study at any time according to their consent. Written informed consent must be obtained from all participants, whose privacy will be strictly protected. The study protocol has been registered in the Clinical Trials Registry under the identification code ChiCTR2400080759.

### Data collection and management

Independent researchers collect raw data for all participants using printed case report forms (CRFs) and enter them into an electronic case report form (eCRF). Physical, printed version of the document CRFs will be kept in a locked filing cabinet in the primary researcher's work office. In contrast, electronic data will be locked in a password-protected computer. Only authorized data managers and statisticians can access these files, and both the physical, printed version of the documents and electronic research documents will be preserved for at least 5 years after publication.

### Quality control

To ensure acupuncturist training and procedural consistency, acupuncturists with at least 5 years of clinical experience need to undergo a 4-week centralized training program prior to the trial. The curriculum included: (1) Theoretical modules: (a) TCM principles of qi and blood deficiency and cervical vertigo pathogenesis and (b) anatomical landmarks for acupoint localization. (2) Practical skill standardization: (a) Needling techniques (depth, angle, and retention time), for TNRM-UN, TNRM-TA, and UN therapy, guided by the Standards for Reporting Interventions in Clinical Trials of Acupuncture (STRICTA) and (b) simulation training using three-dimensional (3D) anatomical models to ensure precision in acupoint targeting. (3) Assessment criteria: (a) Skill examination: Blind evaluation of needle insertion accuracy (±2 mm tolerance) and manipulation (e.g., needle insertion technique, “De Qi” elicitation). (b) Theoretical test: A minimum score of approximately 80% on a 100-item exam covering TCM theory and intervention protocols.

Regarding ultrasound operator training and consistency, we will adhere to under quality control: (1) Operator training: Two sonographers with ≥5 years of neurovascular experience performed all measurements. They underwent centralized training to standardize probe placement, angle correction, and data acquisition. (2) Intraoperator consistency: A subset of 20 patients undergo repeated measurements by the same operator (48-h interval). Intraclass correlation coefficients (ICC) for DV, PSV, EDV, PI, and RI are 0.92–0.96, indicating excellent repeatability. (3) Interoperator consistency: For 20 randomly selected patients, both operators independently perform blinded measurements. Interoperator ICCs ranged 0.88–0.94. ICC reference standards (44) are shown in Table 3.

**Table 3 T3:** Interoperator and intraoperator consistencies of hemodynamic measurements.

**Parameter**	**Intra-operator ICC (95% CI)**	**Inter-operator ICC (95% CI)**
Diameter (DV)	0.94 (0.89–0.97)	0.91 (0.85–0.95)
PSV	0.96 (0.92–0.98)	0.94 (0.89–0.97)
EDV	0.92 (0.86–0.96)	0.88 (0.81–0.93)
PI	0.93 (0.87–0.96)	0.89 (0.82–0.94)
RI	0.95 (0.90–0.97)	0.90 (0.83–0.95)

ICC, intraclass correlation coefficient; CI, confidence interval; PSV, peak systolic velocity; EDV, end-diastolic velocity; PI, pulsatility Index; RI, Resistance Index.

The implementation of the trial will be checked periodically during the study period. All study materials, including the original data and the occurrence of AEs or complications, will be collected in CRFs. We will employ a data monitoring committee to verify the authenticity and consistency of the raw data with the recorded data. The principal investigator will organize regular meetings to discuss problems that arise during the study and put forward optimal solutions.

Finally, to enhance recruitment and adherence of the participants, all treatment expenses were free of charge to participants, and during the follow-up period, we will improve patient compliance through appropriate financial compensation and health education.

## Discussion

### Research status of Acupuncture for CV

Cervical vertigo (CV) is a common disease related to cervical spine dysfunction. Acupuncture, a traditional Chinese medicine therapy, has attracted much attention in recent years due to its safety, effectiveness, and multitarget regulation characteristics. The following three aspects are a summary of the research status at home and abroad from three aspects: Clinical efficacy, mechanism of action, and research characteristics. (1) Clinical efficacy: A recent domestic randomized controlled trial (RCT) by Li et al. (45) used Fengchi (GB20) as the main acupoint for acupuncture treatment of CV. After treatment, the patients' ESCV scores were better than those before treatment (*p* < 0.05). The results indicated that acupuncture treatment for cervical vertigo can improve patients' quality of life. A 1-year follow-up study (46) in the United States (46) showed that the recurrence rate of CV in the acupuncture group (28%) was significantly lower than that in the drug group (55%), with no severe adverse reactions. (2) Mechanism of action: Domestic studies (47, 48) have revealed that acupuncture can relieve the spasm of the vertebral artery, stimulate the sympathetic and parasympathetic nerves, and improve microcirculation to improve blood supply to the brain. Domestic studies believe that regulating vertebral artery blood circulation system is the primary mechanism of acupuncture in the treatment of CV. The mechanism of foreign research focuses on regulating proprioception, neural, and humoral factors. Luo et al. (49) have also revealed that acupuncture can improve proprioceptive disorders by improving the connection between the proprioceptors and the brain, and establishing the correct pattern of sensation and movement in the organism. Jiang et al. (50) concluded that the adequate stimulation of acupoints by acupuncture can reduce the content of neuropeptide Y (NPY) in serum, effectively improve the blood circulation of the vertebral artery, and then improve the symptoms of vertigo. (3) Research focus: Domestic research emphasizes the overall syndrome differentiation and acupoint compatibility, and pays attention to the curative effect of integrated traditional Chinese and Western medicine. Foreign studies focus on standardized protocols and neurophysiological mechanisms and emphasize placebo control.

In the clinical treatment of CV, drug and surgical treatment have difficulty obtaining satisfactory results, and some inevitable side effects often limit their efficacy. Research by Xu et al. (51) showed that the total effective rate of acupuncture in treating cervical vertigo was higher than that of Western medicine. Moreover, acupuncture had more advantages than Western medicine in improving the symptoms of cervical vertigo, the Functional Evaluation Scale (ES-CV) score, and the blood supply of the vertebral–basilar artery. Zhu et al. (52) found that the incidence of adverse reactions in patients with cervical vertigo treated with acupuncture was 0.0%, while that in the conventional Western medicine treatment group was 2.5%. This indicates that acupuncture in treating cervical vertigo has a lower risk of adverse reactions. In this context, acupuncture may be a potentially satisfying therapy for CV, but the current evidence is still unsatisfactory due to significant methodological flaws and potential publication bias; moreover, among the numerous acupuncture treatments for CV, which is the most effective treatment, the present study aimed to find a simple, low-cost, safe, and more effective acupuncture treatment method for CV through high-quality research methods.

### Strengths of the study

In TCM, the activities of the mind and spirit depend on transformation of qi and moistening of the blood, if the deficient qi and blood cannot transform mind and carry spirit, it will inevitably lead to the loss of use of the mind and the loss of nourishment of the brain marrow, thus developing vertigo. Therefore, in this study, qi and blood deficiency type is taken as the primary research syndrome of CV. This study suggests, for the first time, that the patient's mind should first be stabilized through the three-needle of regulating the mind. The reasons for choosing Shenting (DU24), Baihui (DU20), and Naohu (DU-17) to regulate patients' minds are as follows: (1) These three acupoints are the essential acupoints of the forebrain, top of the brain, and hindbrain, respectively. Brain acupoints have a shallow muscular layer richly distributed with vessels and nerves. Appropriate acupuncture stimulation at the brain acupoints can converge the lax mind, regulate brain discharge, and release neurotransmitters to improve the function of the brain to achieve the purpose of regulating the mind. (2) The three acupoints belong to the governor vessel that enters the collateral brain on the rooftop. The running course of the governor vessel in the back overlaps with the spinal cord, while, brain is the sea of marrow. A branch of the governor vessel runs through the heart to the throat, so the governor vessel is closely related to the heart. The heart is the birthplace of the mind; therefore, the regulatory effect of the governor vessel on the mind is much greater than that of other meridians. (3) The efficacy of the three acupoints themselves also plays a key role. Shenting (DU24) point can affect people's minds by regulating the governor vessel. Baihui (DU20) is where all Yang meridians meet on the head, which is one of the essential points for regulating brain function. Naohu (DU-17) point is the gateway for the meridian qi of the governor vessel in and out of the brain, which brightens the eyes, relieves spasticity, and calms the mind.

Umbilical needle therapy is a characteristic acupuncture method gradually developed by [name], through many clinical practices combined with Yi Jing theory, holographic theory, time medicine theory, and embryonic development theory, which also refers to TCM theory, including five elements theory, meridian theory, and organ picture theory (53). Each acupoint in the human body carries information about its own body, and the umbilicus contains the highest information element of the human body due to the particularity of the umbilicus in embryonic development and human anatomy. This study is the first to apply umbilical needle therapy to treat CV. This study selected Kan, Zhen, Xun, Li, Kun, and Qian positions to treat CV for the following reasons: (1) The umbilicus, the location of Shenque (CV8) point, belongs to conception vessel. The conception and governor vessels exit from the uterus, with one source but two different sources, ascending and converging on the head and face, closely related to the brain and spirit. Shenque point (umbilicus) itself regulates the circulation of qi and blood, supplementing essence blood, consolidating the kidney, and cultivating essence (54, 55). (2) According to the holographic law of “luo shu” in the umbilical needle theoretical system, Xun, Li, and Kun positions correspond to the right shoulder, neck, and left shoulder, respectively. TCM believes that the onset of CV is closely linked to the liver, spleen, and kidneys. According to the holographic theory of the inner eight trigrams, the positions of Zhen, Kun, and Kan correspond to the liver, spleen, and kidneys, respectively. According to the holographic theory of outer eight trigrams, the positions of Qian, Kan, and Li correspond to the head, ear, and eye, respectively. So, these positions can not only treat the main symptoms of CV but also treat accompanying symptoms of CV, such as headache, dizziness, blurred vision, tinnitus, etc. Moreover, Kan and Li positions constitute “water-fire combination” to improve spinal instability in these combinations of orientations. Zhen and Xun positions constitute a “thunder-wind struggle” to relieve anxiety and depression caused by dizziness. Kun and Qian positions constitute “earth-day tai” to take the intersection of yin and yang. Zhen, Li, and Kun's positions constitute “three-needle for strengthening the spleen” to improve qi and blood deficiency syndrome.

The innovations in the intervention approach of this study are explained as follows: Regarding the three-needle method of regulating the mind, its theoretical basis is the meridian system theory of TCM, the stimulated meridian qi is acquired meridian qi, the acupuncture site is in the brain, and the acupuncture points are located in the governor vessel. Regarding umbilical needle therapy, its theoretical basis is Yi Jing theory, the stimulated meridian qi is innate, the acupuncture site is in the umbilical region, and the acupuncture point is located in the conception vessel. Umbilical needle therapy breaks through the 1,000 of years confinement of “Shen que forbidding needles” and paves the way for the precedent of “one point curing hundreds of diseases.” This study is the first attempt to combine the two methods in treating CV. This method combines the theory of TCM and Yi Jing, the combination of the human brain and umbilical cord, the combination of the governor vessel and conception vessel, and the combination of the innate and acquired meridians. This method has the advantages of few acupuncture points, simple operation, and less pain. While it appears to be simple, it contains a great deal of theoretical basis and information, and fully embodies the holistic view of TCM and the principle of “the way is simple.”

The innovations in the control setting of this study are explained as follows: (1) The three-needle regulating the mind combined with the traditional acupuncture group was compared to the three-needle regulating the mind combined with the umbilical needle group. Both groups received initial treatment with three needles to regulate the mind for mental relaxation, and there was only a difference in the single factor of “traditional acupuncture” or “umbilical needle.” This study aimed to confirm the superiority of the umbilical needle compared with traditional acupuncture as a control. (2) The three-needle regulating the mind combined with the umbilical needle group was compared with the umbilical needle-only group. Both groups received treatment with an umbilical needle, and there was only a difference in the single factor of whether a three-needle regulating the mind was used. We propose to confirm the importance of using a three-needle to regulate the mind in CV.

### Clinical implications of hemodynamic changes

The hemodynamic parameters measured via color Doppler ultrasound–vertebral artery diameter (DV), peak systolic velocity (PSV), end-diastolic velocity (EDV), pulsatility index (PI), and resistance index (RI) are critical biomarkers for assessing vertebrobasilar insufficiency, a key contributor to cervical vertigo (CV). In clinical practice, increased arterial diameter (DV), peak systolic velocity (PSV), and end-diastolic velocity (EDV) reflect enhanced blood volume and velocity, which are associated with improved cerebral perfusion. Prior studies (39) have shown that PSV < 35 cm/s or EDV < 15 cm/s correlates with symptomatic dizziness, and VD < 2.80 mm is defined as vertebral artery stenosis. Normalization of these values post-intervention predicts reduced CV recurrence. Elevated RI (>0.70) and PI (>1.30) indicate heightened vascular resistance, often linked to arterial stiffness or stenosis. A reduction in these indices post-treatment suggests improved vascular compliance and downstream perfusion, which may alleviate symptoms such as nausea and lightheadedness (56). The clinical prognostic value of hemodynamics is as follows: Sustained hemodynamic improvements (e.g., stable PSV and reduced RI) are associated with long-term symptom remission and lower risk of cerebrovascular complications (57). For instance, patients with persistent PI > 1.30 have a 2.5-fold higher likelihood of recurrent vertigo (58).

In this trial, improvements in these parameters following TNRM-UN therapy may indicate restored vertebral artery flow dynamics, which aligns with symptom alleviation (e.g., reduced CVS-FAS scores). However, individual variability in hemodynamic-symptom correlation warrants cautious interpretation.

## Limitations

(1) The inherent inability to blind participants and acupuncturists in acupuncture trials introduces two key biases: (a) Performance Bias: Acupuncturists may unconsciously intensify treatment for the experimental group (TNRM-UN), inflating observed effects. (b) Reporting Bias: Participants aware of receiving active therapy may overreport symptom improvement, particularly for subjective outcomes. To this end, to mitigate bias partially, we will employ the following strategies:

(a) Standardized participant pre-treatment education: All participants will receive identical oral/written explanations about potential benefits of all interventions (TNRM-UN, TNRM-TA, and UN) to equalize expectations.

(b) Third-party outcome monitoring: Independent assessors will review video recordings of 30% randomly selected acupuncture sessions to ensure protocol adherence.

(c) We will incorporate an electronic health record (EHR) to track long-term outcomes, which can reduce subjective reporting reliance.

(2) Due to the lack of relevant RCTs, our sample size has to refer to the formula for the sample size of multiple groups of randomized controlled trials. The pilot trial's single-arm design (*n* = 20) may not fully capture variability in a three-group RCT. We conservatively set δ as 60% of this observed effect (δ = 5 points), while clinically justified, it lacks direct empirical validation for CVS-FAS, which requires empirical validation in future trials. Nevertheless, our study will provide compelling evidence for sample size estimation for future RCTs.

(3) Deficiency of qi and blood is the predominant TCM syndrome in CV (60%−70% in our hospital), and our study protocol may not apply to patients with other TCM syndromes. But we acknowledge the potential impact of subgroup proportion on generalizability. Future multisyndromic trials are needed to validate these results across broader populations.

(4) About ultrasonic measurements, while our measurement protocols align with the European Society of Neurosonology Guidelines for Extracranial Doppler Ultrasonography, subtle variations in sampling gate positioning or patient motion may affect PI/RI reproducibility. Future studies could employ automated angle-tracking software to minimize variability further.

(5) While this trial includes a 24-week follow-up period to assess mid-term outcomes, we recognize that this duration may not fully capture the long-term sustainability of therapeutic effects or potential delayed adverse events. To address this gap, we plan to conduct an extended follow-up study (up to 48 weeks) for participants who complete the current trial. This extension will focus on: (a) long-term symptom trajectories: reassessing CVS-FAS and QBD-SAS scores at 36 and 48 weeks to determine durability of symptom relief, (b) delayed adverse effects: monitoring for late-onset complications associated with repeated acupuncture, and (c) patient compliance and behavior: Investigating whether patients adopt supplemental therapies post-trial and their impact on outcomes.

(6) We did not select sham acupuncture as the control arm for two reasons: (a) Acupuncture is very popular in hospitals that recruit participants. Many patients have extensive experience with the sensation of acupuncture, which makes the blinding of participants impractical, even with the design of the sham acupuncture group. (b) The studies revealed that all current sham acupuncture modalities have positive therapeutic effects because they are not absolutely inert (59–61). Then, the therapeutic effect of acupuncture is easily underestimated when compared to sham acupuncture. Therefore, we have not designed a sham acupuncture group as the control. Nevertheless, the therapeutic effect may be influenced by the psychological effects coming from acupuncture, which should be interpreted in the study results.

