### Discontinuation or elimination criteria

(1) Participants were mistakenly included in the trial.

(2) Participants experienced serious adverse events (AEs) and did not consistently participate in the study.

(3) Participants suffered serious complications during the course of the trial, which required emergency care.

(4) Participants with personal factors were asked to stop the trial.

(5) Participants with poor compliance did not adhere well to the study process.

(6) The participants received treatment outside the intervention.

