### Safety evaluation

Acupuncture-associated adverse events (AEs) include intolerable pain, bleeding, local hematoma, and other uncomfortable feelings after acupuncture (e.g., pale face, cold, moist limbs, cold sweat, dizziness, nausea, rapid heartbeat, weak pulse, and even fainting). All AEs, which will be considered as unrelated, possibly related, or related to treatment, will be recorded and assessed by investigators on an adverse event. Investigators should record in detail the occurrence date, degree [mild, moderate, or severe (41)], duration of symptoms, and emergency measures of AEs.

Timely rescue measures will be taken for serious adverse events. Simultaneously, researchers will immediately report to the Ethics Committee, which will decide whether to withdraw the participants from the study.

To comprehensively assess delayed-onset AEs and acupuncture safety, we will take the following measures: (1) Extended follow-up duration: Participants will receive monthly telephone follow-ups for 6 months post-trial completion (up to week 48) to capture delayed-onset AEs. (2) Patient-reported outcome diaries: Participants will document daily symptoms (e.g., pain and numbness) in a standardized diary for 12 weeks post-treatment. (3) Electronic Health Record (EHR) Linkage: With participants' consent, we will access electronic health records for a 1-year post-trial to identify their hospitalizations or diagnoses potentially linked to acupuncture.

Standardized Criteria for AE Causality Assessment will adopt the following measures: (1) WHO-UMC Causality Criteria (42): (a) Certain: AE occurs post-treatment, aligns with known acupuncture effects, and resolves upon discontinuation. (b) Probable/likely: Temporal association with no confounding factors. (c) Possible: Plausible link, but alternative explanations exist. (d) Unlikely: No plausible connection to treatment. (2) Naranjo algorithm (43): A quantitative tool to score causality likelihood (scores: ≥5: “probable”; ≤ 1: “doubtful”). (3) Independent adjudication: A blinded Safety Review Board (SRB) comprising a neurologist, TCM expert, and pharmacovigilance specialist will resolve disputed cases.

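### Week-48 follow-up for delayed harms covers participants in one section but only completers in another, so people discontinued for serious events may get no active late-harm contact

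*Protocol article*

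**What the plan says.** Three places in the protocol article bear on who is followed for late harms.

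- **Safety evaluation.** Among the measures for delayed-onset events: "Participants will receive monthly telephone follow-ups for 6 months post-trial completion (up to week 48) to capture delayed-onset AEs". The subject of the sentence carries no completer restriction, but the start of the calls is tied to trial completion. The same section adds a diary ("Participants will document daily symptoms (e.g., pain and numbness) in a standardized diary for 12 weeks post-treatment") and, with consent, record linkage ("we will access electronic health records for a 1-year post-trial to identify their hospitalizations or diagnoses potentially linked to acupuncture"). Neither is worded as limited to completers.
- **Limitations, item (5).** The authors say that the 24-week follow-up may not fully capture delayed adverse events. To close that gap, "we plan to conduct an extended follow-up study (up to 48 weeks) for participants who complete the current trial". One of its three stated aims is "delayed adverse effects: monitoring for late-onset complications associated with repeated acupuncture".
- **Table 1.** Safety evaluation is marked at weeks 6, 12 and 24 and at no later time.

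Two of the six discontinuation or elimination criteria concern harm: "Participants experienced serious adverse events (AEs) and did not consistently participate in the study" and "Participants suffered serious complications during the course of the trial, which required emergency care". The safety section also sends serious events to the Ethics Committee, "which will decide whether to withdraw the participants from the study". Nowhere does the article say that a discontinued participant stays in safety follow-up.

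**The concern.** The two sections describe the same window and the same purpose but different populations. One version selects on having finished the trial, and some people do not finish because they were harmed. A late-harm rate taken from completers describes those who tolerated the treatment well enough to stay, and so tends to be too low.

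The comparison between arms is also exposed. The arms needle different sites (scalp plus umbilicus; scalp plus neck and back; umbilicus alone), so discontinuation for harm could differ between them. An arm that lost more people to harm would then look safer late on for that reason alone. Safety is a stated objective in both the Abstract and the Conclusion.

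**Working it through.** The plan gives no figure to reproduce here. The check is a comparison of passages with two small calculations.

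**1. Is it the same window?** Table 1 places the last trial visit at week 24. Six months of four weeks gives 24 + 6 × 4 = 48, which matches both sections. Six calendar months would give about 24 + 26 = week 50. Both sections therefore describe follow-up from about week 24 to week 48.

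**2. Is it the same purpose?** Yes for harms: delayed-onset adverse events in the safety section, delayed adverse effects in Limitations (5). The extension also reassesses the two symptom scales at weeks 36 and 48 and looks at supplemental therapies.

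**3. Who is covered under each reading?**

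| Reading | Calls in Safety evaluation | Extension in Limitations (5) | Person discontinued for a serious event |
|---|---|---|---|
| Trial completion means the trial's fixed week-24 end | All participants | Completers | Called under one section, excluded under the other |
| Trial completion means each participant's own completion | Completers | Completers | No late calls under either section |

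On the first reading the sections disagree. On the second they agree more closely, but the gap in harm follow-up is firmer. Both need a change of wording.

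**4. What else could detect a late harm in a discontinued person?** Record linkage runs for one year after the trial. It needs consent and finds only events that reach a record as a hospitalization or diagnosis. The diary runs 12 weeks after treatment; for someone treated to week 6 it ends at about 6 + 12 = week 18, before the week-24 to week-48 window opens.

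**5. How many people?** Inputs from Sample size estimation: 33 enrolled and 30 required per group, 10% dropout. Non-completers: 33 − 30 = 3 per group, and 99 − 90 = 9 in total. This is all-cause dropout. The documents do not say what share would stop for harm.

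**6. What does it cost in precision?** With zero late events among n people, the exact one-sided 95% upper bound is 1 − 0.05^(1/n).

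- n = 99: 1 − 0.05^(1/99) = 2.98%
- n = 90: 1 − 0.05^(1/90) = 3.27%

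The difference is 0.29 percentage points. The issue is which people are missing, not how many.

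**The case against.** The strongest reply is that the safety section is the operative text and commits to calling participants, while Limitations (5) describes a further study with wider aims. A later study open only to completers need not narrow the safety measures. The article does not say that the two are separate activities, however. It also presents the completer extension as the answer to the trial's own inability to capture delayed adverse events. That ties it to the same task, so it cannot be set aside as unrelated.

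Several other objections stand and limit the point:

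- A reader might infer that the calls can never start for a discontinued participant. That is only one reading of trial completion; the fixed week-24 end fits the week arithmetic at least as well.
- A reader might infer that discontinued people are lost to all late-harm detection, or that their events would have no recorded outcome. The text does not support this. Record linkage and the diary are not limited to completers, serious events are reported immediately, and investigators must record the duration of each adverse event.
- A reader might build a worst case in which all 3 non-completers in an arm carry the late events, so that completers show 0/30 against a true 3/33 = 9.1%. Nothing in the documents supports that. The 10% is an all-cause planning figure, and the discontinuation list also covers mistaken inclusion, personal reasons, poor compliance and outside treatment. Even then, the upper bound for 0/30, 1 − 0.05^(1/30) = 9.5%, would include 9.1%.
- Table 1 ending at week 24 is not an error in itself, because the calls are described as following the trial. It simply does not resolve the difference.

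An article may leave details of off-treatment contact to the full protocol. Here, though, it states the late-harm population twice, in terms that do not match.

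**Conclusion.** The point holds in a limited form. The article leaves it unclear whether people discontinued for serious events or complications receive the week-48 safety calls, and one of its two statements excludes them. Under the Limitations (5) rule, or if trial completion is personal, late-harm comparisons between arms could be selectively biased low. Record linkage and the diary reduce the loss without removing it.

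Up to about 9 of 99 participants would be outside a completer-only extension, assuming dropout occurs at the planned 10%. The number stopping for harm is unknown, so the size of any bias cannot be computed from the documents; the effect on precision is negligible. The primary outcomes and the scheduled safety assessments at weeks 6, 12 and 24 are not affected by this point. It should be corrected because safety is an objective and the correction is cheap.

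**What to change.** Reconcile Safety evaluation, Limitations (5) and Table 1 around one rule for collecting late-safety data:

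- The monthly safety calls to week 48 cover every treated participant, timed from randomisation, whether or not the person completed or was discontinued, unless consent to contact is withdrawn.
- Table 1 shows these calls after week 24.
- Late harms are reported by arm for all treated participants.
- The completer restriction may stay for the symptom scales at weeks 36 and 48.

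This concerns data collection only and leaves the discontinuation criteria and clinical management as they are. The cost is revised wording in two sections, added columns in Table 1, and monthly calls to about nine more people.
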